#### Secondary outcomes

Time to diagnosis: The time interval between a woman’s first visit to a health facility and her confirmed breast diagnosis will be measured using clinical records from the app (intervention group) and patient medical records (control group). Descriptive statistics (mean, median, interquartile range, and standard deviation) will be used to summarise the time intervals in both groups. Time to diagnosis will be dichotomised as ≤60 days timely versus >60 days delayed and analysed using multivariable mixed-effects logistic regression adjusting for potential confounders and accounting for clustering at the health facility level.

Proportion of internal referrals and proportion of early-stage breast cancer diagnoses: Descriptive statistics (percentages) will be used to summarise these proportions. Comparisons between the intervention and control arms will be conducted using multivariable mixed-effects logistic regression accounting for clustering at health facility level and adjusting for possible confounders.

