### Participant timeline {13}

Following randomisation, eligible participants visiting the study health facilities are being enrolled (Table 1). In the intervention arm, referral details are being registered and tracked through the DINKNESH referral and follow-up app. Feedback is being recorded upon the patient’s arrival at the referral facility, marking the end of the participant’s study period. In the control arm, referrals are following routine care procedures, and medical records are being reviewed 60 days after referral to assess diagnosis and feedback. The 60-day cutoff for each study participant is based on GBCI recommendations for timely diagnosis [5].

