#### Secondary outcomes

The time interval between a woman’s first visit to a health facility and her confirmed breast diagnosis, the proportion of internal referrals within the facility, and the proportion of detected early-stage breast cancers will be assessed. These data will be captured through clinical information recorded in the app and the patient’s medical records. The proportions for each of these secondary outcomes will then be calculated.

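### Raw summaries of time to diagnosis are right-truncated at the 60-day reading, intervention follow-up is stated to end at arrival, and the binary outcome needs a rule for undiagnosed women

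*Protocol article*

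**What the plan says.** All references are to the protocol article.

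- **Analysis.** Statistical methods {20a}, Secondary outcomes, counts time from first visit to confirmed diagnosis, with the app as source in the intervention arm and medical records in controls. "Descriptive statistics (mean, median, interquartile range, and standard deviation) will be used to summarise the time intervals in both groups". Then "Time to diagnosis will be dichotomised as ≤60 days timely versus >60 days delayed", analysed by mixed-effects logistic regression.
- **Control ascertainment.** Participant timeline {13}: "medical records are being reviewed 60 days after referral to assess diagnosis and feedback". Plans for assessment {18a} gives the same 60-day timing for the review of control records.
- **Intervention ascertainment.** Participant timeline {13}: "Feedback is being recorded upon the patient’s arrival at the referral facility, marking the end of the participant’s study period".
- **Window.** The same section adds: "The 60-day cutoff for each study participant is based on GBCI recommendations for timely diagnosis". The Discussion also describes follow-up as 60 days.
- **Data source in the outcome section.** Secondary outcomes under {18a}: "These data will be captured through clinical information recorded in the app and the patient’s medical records", with no split by arm and no reading date.
- **Missing data {20c}.** All enrolled women are to be analysed by intention to treat, the method will depend on the type of missingness, and a sensitivity analysis is planned. Women still undiagnosed when observation ends are not mentioned.

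**The concern.** Three statements do not fit together: interval summaries that need a diagnosis date for every woman, a reading at 60 days after referral, and an intervention study period that closes at arrival.

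A woman without a confirmed diagnosis when her records are read has no interval. The mean, SD, median and IQR can then be computed only among women diagnosed in time to be seen. Membership of that group is decided after randomisation, and the app is meant to change it. Comparing intervals within it is no longer a comparison of the randomised arms, and long intervals are removed from both.

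The second problem is unequal observation. Controls are read at a fixed day. Intervention women are, on the literal wording, observed until arrival, which would normally come before a confirmed diagnosis. Diagnoses could then be captured less completely in one arm.

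The third is the binary outcome. The plan does not say whether an undiagnosed woman counts as delayed or is left out. At stake is the secondary outcome closest to the trial's aim of reducing diagnostic delay.

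**Working it through.** The plan gives no power, event count or expected distribution for time to diagnosis, so there is no figure of its own to reproduce. The check has three parts.

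**1. Truncation of the summaries (illustration)**

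Inputs: the 60-day reading (Participant timeline {13}), and 52% and 70% from Objectives {7}. Those two are referral-completion rates; using them as the proportion q diagnosed by day 60 is an assumption. So are the shape of the distribution and referral on the day of first visit.

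Exponential model, rate r = −ln(1 − q)/60:

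- q = 0.52: r = 0.7340/60 = 0.01223 per day
- q = 0.70: r = 1.2040/60 = 0.02007 per day

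True median = ln 2/r. Median among those diagnosed by day 60 = −ln(1 − q/2)/r. True mean = 1/r. Mean among those diagnosed by day 60 = 1/r − 60(1 − q)/q. A log-normal model with log-SD 1 was run as a second shape.

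| Model | Statistic (days) | q = 0.52 | q = 0.70 | Difference |
|---|---|---|---|---|
| Exponential | true median | 56.7 | 34.5 | 22.1 |
| Exponential | median seen by day 60 | 24.6 | 21.5 | 3.1 |
| Exponential | true mean | 81.7 | 49.8 | 31.9 |
| Exponential | mean seen by day 60 | 26.4 | 24.1 | 2.2 |
| Log-normal | true median | 57.1 | 35.5 | 21.6 |
| Log-normal | median seen by day 60 | 30.0 | 24.2 | 5.8 |
| Log-normal | true mean | 94.1 | 58.6 | 35.5 |
| Log-normal | mean seen by day 60 | 31.0 | 26.5 | 4.4 |

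The observed means stay between about 24 and 31 days whether the true mean is about 50 or about 94.

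**2. The split at 60 days**

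Over 60 days is the complement of diagnosed by day 60, so it needs no later diagnosis date. Referral cannot precede the first visit, so a review 60 days after referral covers the full 60 days from first visit in controls.

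- Undiagnosed women counted as not timely: the same inputs give 48% and 30% delayed, and the contrast is intact.
- Only women with a dated diagnosis analysed: with a lag of L days from first visit to referral, the share recorded as over 60 days is (e^(−60r) − e^(−(60+L)r)) / (1 − e^(−(60+L)r)). Under the exponential model:

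| L (days) | q = 0.52 | q = 0.70 |
|---|---|---|
| 0 | 0% | 0% |
| 7 | 7.0% | 5.3% |
| 14 | 12.7% | 9.5% |

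So the model stands or falls on a coding rule that is not stated.

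**3. The end of intervention follow-up**

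Participant timeline {13} ends the intervention participant's study period at arrival, an event. The same section sets a 60-day cutoff for every participant. Secondary outcomes under {18a} and {20a} require a confirmed diagnosis for intervention women, which would normally come after arrival. These statements cannot all be followed literally.

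**The case against.** A reader might infer that the outcome cannot be analysed at all, that the over-60-day category is itself truncated, that nearly every woman would be classed as timely, or that the app's effect could be reversed. The documents do not support this. The only between-arm model planned for this outcome is the logistic one, and in controls its indicator is fully observed by the day-60 review. Missing data {20c} says all enrolled women are analysed, and nothing says undiagnosed women are dropped. The near-empty category arises only if they are. The illustration shows attenuation in the same direction, and no calculation supports a reversal. Nor are later diagnoses wholly unseen: the interval runs from first visit and the review from referral, so any lag brings some into view.

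On the intervention arm, the arrival wording is one sentence set against others that point to a 60-day window and to medical records as a source. It shows an inconsistency, not that diagnoses will go unrecorded.

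Coding and censoring rules are also commonly left to an analysis plan, which is not shown. That is fair for the coding of undiagnosed women taken alone. It does not answer the other two points, because the article itself names the raw summaries, the 60-day reading and the end at arrival. The summaries are descriptive and the outcome is secondary, which limits the weight of the point but does not remove it.

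**Conclusion.** The concern holds in a limited form. Followed as written, the mean, SD, median and IQR of time to diagnosis are right-truncated, and the statements on when intervention follow-up ends conflict, so ascertainment may differ by arm. The logistic analysis is sound provided undiagnosed women count as not timely.

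Truncation follows under any distribution in which some diagnoses come after the reading. Its size is not known from the documents. The shrinkage of a 22-day difference in medians to about 3 days (exponential) or 6 days (log-normal) rests on assumed distributions, borrowed referral-completion rates and no referral lag, and should be read as illustration only. Neither the general missing-data statement nor the unsplit list of data sources resolves the point. It should be settled before analysis, but it does not touch the primary outcome.

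**What to change.** 1. Define the binary outcome as confirmed diagnosis within 60 days of first visit (yes/no), with all enrolled women in the denominator and women undiagnosed by then counted as not timely. Keep the planned mixed-effects logistic model.
2. Replace the mean, SD and raw medians with Kaplan-Meier or cumulative-incidence estimates by arm from first visit, censoring undiagnosed women at the record-review date. Report a median only where at least half the arm is diagnosed within the window.
3. Reconcile Participant timeline {13} with Secondary outcomes under {18a} and {20a}, so that diagnosis status is ascertained over the same 60-day window in both arms. Step 2 depends on this: censoring intervention women at arrival would tie censoring to progress towards diagnosis.

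Cost: steps 1 and 2 are wording. Step 3 adds some data collection, since the existing data collectors would check day-60 records for intervention women whose diagnosis is not in the app. Enrolment began on 30 November 2024, so women already past day 60 would need their records read retrospectively, using dated entries up to the same cutoff.

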**Discussion:**

This study will provide robust evidence on whether app-based referral systems for women with breast symptoms can improve follow-up and facilitate early breast cancer detection in low-resource settings such as Ethiopia. The findings will support the WHO Global Breast Cancer Initiative’s goal of diagnosing more than 60% of breast cancer cases at an early stage.

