## Objectives {7}

The primary objective of this study is to evaluate the effectiveness of the DINKNESH referral and follow-up app in enhancing referral completion for women with breast-related abnormalities at primary healthcare settings in Ethiopia, specifically by determining the proportion of successfully completed referrals.

Hypothesis: The use of the DINKNESH referral and follow-up app will increase the proportion of completed referrals from 52% to 70% for women with breast-related abnormalities after undergoing a CBE compared with the routine standard referral process.

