#### Inclusion criteria

Women aged ≥18 years presenting with a self-reported breast-related abnormalityWomen aged ≥30 years visiting the health centre outpatient department who are willing to undergo CBE and have an abnormal clinical finding (based on the recent Ethiopian breast cancer guideline [19])

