### Sample size {14}

The sample size was calculated following established methods for cluster randomised trials [21]. The calculation aimed to detect an increase in the proportion of complete referrals from 52% (based on a study in Tanzania [22]) to 70% in the intervention group. Using 80% power and a 5% significance level, and assuming an intra-cluster correlation coefficient of 0.01, the sample size was adjusted for clustering. With 8 clusters (4 intervention and 4 control) and equal allocation, the required sample size under individual randomisation was 222. After adjusting for the design effect due to clustering, the total required sample size increased to 282, corresponding to approximately 35 individuals per cluster.

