### Recruitment {15}

All women with self-reported or CBE-detected breast abnormalities are being invited by trained staff at the health facilities to voluntarily participate in the study. Enrolment will continue until the required sample size of 35 participants is reached at each clustered facility. Once the target number is achieved, no additional participants will be included.

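### Stage among detected cancers is compared by a multivariable mixed model, although detection comes after randomisation on the pathway the app is meant to change, and the cancers will probably be few

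*Protocol article*

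**What the plan says.** Outcomes {12} lists the early-stage share of detected breast cancers as a secondary outcome, so the denominator is women in whom cancer has been diagnosed. The Secondary outcomes part of Statistical methods {20a} first summarises this share, and the share of internal referrals, by percentages, and then adds: "Comparisons between the intervention and control arms will be conducted using multivariable mixed-effects logistic regression accounting for clustering at health facility level". The model also adjusts for confounders that are not named.

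The women enrolled are those with a breast abnormality of any kind. They either report one themselves or are aged 30 or over, "who are willing to undergo CBE and have an abnormal clinical finding". Recruitment {15} fixes the number: "Enrolment will continue until the required sample size of 35 participants is reached at each clustered facility".

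Sample size {14} serves the primary outcome only. The hypothesis in Objectives {7} is that the app "will increase the proportion of completed referrals from 52% to 70% for women with breast-related abnormalities". It works through reminders to patients and advance notices to the receiving facility (Interventions).

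Participant timeline {13} ends the intervention-arm study period when feedback is recorded on arrival at the referral facility. In the control arm, records are reviewed 60 days after referral. Plans for assessment and collection of outcomes {18a} takes the secondary outcomes from the app and the medical records.

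**The concern.** There are two separate difficulties.

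The first is the denominator. A woman enters this comparison only if her cancer is diagnosed, and the trial is built on the expectation that more women reach diagnosis in the app arm. If the app works as hoped, the two groups of diagnosed cancers may have been selected differently. A difference in stage mix could then reflect who was diagnosed and not earlier detection. Adjusting for baseline covariates does not undo a selection made after randomisation.

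The second is the amount of data. The trial enrols women with abnormalities, most of whom may not have cancer, and stops at 35 per facility. A multivariable model with a facility effect may be fitted to very few cancers.

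This is the only stage outcome, and the abstract says: "This study will provide robust evidence on whether app-based referral systems for women with breast symptoms can improve follow-up and facilitate early breast cancer detection". A reader is likely to look to this comparison for the early-detection part of that sentence.

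**Working it through.** **Inputs from the protocol.** 8 facilities, 35 women each, so 8 × 35 = 280; completion 52% v 70%; 80% power, 5% significance, intra-cluster correlation 0.01 (Sample size {14}); background early-stage rate 34.2% and target 60% (Background {6a}).

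**Assumptions.** The cancer yield is not given; 5% to 15% is the main range, extended to 30%. The completion rates stand in for the share reaching diagnosis, with mean (52 + 70)/2 = 61%. This is a proxy, because a completed referral also requires feedback.

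**The plan's own figure.** Per arm, (1.96 + 0.84)² × (0.52 × 0.48 + 0.70 × 0.30)/0.18² = 111.3, or 222.7 in total, against 222 stated. The design effect with 222/8 = 27.75 per cluster is 1 + 26.75 × 0.01 = 1.2675, and 222 × 1.2675 = 281.4, matching the stated 282. These figures concern referral completion only.

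**Selection.** Let the true early-stage share be 34.2% in both arms, and let the app arm complete 70% whatever the stage.

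- Control completion 40% for early and 58.2% for late cancers: overall 0.342 × 0.40 + 0.658 × 0.582 = 0.520. Observed early share = 0.1368/0.520 = 26.3%, against 34.2% with the app. The odds ratio is 58.2/40 = 1.455, or about 1.45.
- Control completion 60% early and 47.8% late: overall again 0.520. Observed early share = 0.2052/0.520 = 39.5%, and the odds ratio is 47.8/60 = 0.80.
- Completion unrelated to stage in both arms: odds ratio 1.0.

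**Number of cancers.** Cancers = 280 × yield, then × 0.61. Early-stage cases = that × 0.342.

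| Assumed yield | Cancers, all diagnosed (per facility) | Cancers, 61% diagnosed (per facility) | Early-stage cases, 61% diagnosed |
|---|---|---|---|
| 5% | 14 (1.8) | 8.5 (1.1) | 2.9 |
| 10% | 28 (3.5) | 17 (2.1) | 5.8 |
| 15% | 42 (5.3) | 26 (3.2) | 8.8 |
| 20% | 56 (7.0) | 34 (4.3) | 11.7 |
| 30% | 84 (10.5) | 51 (6.4) | 17.5 |

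**Precision, clustering ignored and all women diagnosed.** The 95% half-width for the arm difference is 1.96 × √(2 × 0.342 × 0.658/n). With n = 7, 14 and 21 per arm it is 50, 35 and 29 percentage points. Power for 34.2% v 60% is 15%, 27%, 49% and 66% at yields of 5%, 10%, 20% and 30%. Reaching 80% takes 58 cancers per arm, or 116/280 = 41% of all women enrolled.

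**Can the model be fitted?** In 1000 simulated trials per scenario, a logistic model with arm, facility type and three covariates was checked for separation. The three covariates are an assumption. The model was separated or not estimable in:

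| Assumed yield | 61% diagnosed | All diagnosed |
|---|---|---|
| 5% | 95% | 69% |
| 10% | 53% | 15% |
| 15% | 20% | 3% |
| 20% | 8% | 0.5% |
| 30% | 1% | 0% |

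**The case against.** The strongest reply has five parts.

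- **Model failure is not certain.** A reader might infer that the model will break down and give meaningless odds ratios. The documents do not support that. Neither the yield nor the number of covariates is stated, outright failure is uncommon at 20% to 30%, and a random-intercept variance estimated at zero only returns an ordinary logistic regression. A penalised or reduced model may also be left to an analysis plan that is not shown.
- **The stage mix need not shift.** A reader might infer that selection alone must move it. It does so only if completion depends on stage differently by arm, and the protocol says nothing on that.
- **Stage may well be collected.** A reader might infer from Participant timeline {13} that intervention-arm follow-up stops before stage is known. But {18a} uses the medical records as well as the app, and {20a} measures time to confirmed diagnosis in that arm. The passages need reconciling; they do not show that stage is missing.
- **The denominator wording varies.** {18a} and {20a} can be read less strictly than Outcomes {12}. With all enrolled women as denominator the selection point would fall away, but early-stage cases would be just as few.
- **Low power for a secondary outcome is ordinary.** That is true, and it is not the fault raised here.

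What remains is the denominator as Outcomes {12} defines it, and the choice of an adjusted comparative model for it.

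**Conclusion.** The point stands in a conditional form. That the contrast is not protected by randomisation follows from the protocol's own definition and hypothesis and needs no outside figure. The size and direction of any bias are unknown; odds ratios of about 1.45 and 0.80 are illustrations under assumed completion rates.

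Imprecision is likely throughout the assumed 5% to 15% yield. Failure of the fit is a material risk at the lower yields, given about five model terms.

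The point concerns one secondary outcome. The quoted sentence also covers internal referrals, to which none of this applies, and the primary analysis is untouched. Nor does it require the abstract's sentence to be struck out, since that sentence also covers follow-up, which the primary outcome addresses. A conclusion about early-stage detection should simply not rest on the stage share among detected cases.

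**What to change.** 1. Make the between-arm comparison early-stage cancers per enrolled woman and all cancers per enrolled woman, allowing for clustering. Both are needed, because early-stage cases can rise simply because more cancers of every stage are found. Enrolment itself follows cluster allocation, but this denominator is fixed before the app acts on the referral.
2. Report stage among detected cancers descriptively: counts by stage and arm with exact intervals, without the multivariable model.
3. Reconcile Participant timeline {13} with {18a} and {20a}, so that stage comes from the same record review over the same window in both arms.
4. State that no conclusion about early-stage detection will be drawn from the stage share among detected cancers.

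The cost is the adjusted odds ratio for this secondary outcome, together with any extra record review needed in the intervention arm. No further recruitment or design change is needed. The per-woman comparison will not be more precise, because the early-stage cases are the same few; its gain is comparability.

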#### Qualitative assessment

The audio-recorded interviews will be transcribed and translated into English. Coding of the translated interviews will be conducted using OpenCode software for qualitative data analysis (version 4.03). The RE-AIM framework will guide the analysis of the qualitative data [25]. Coded interviews will be categorised and sub-categorised based on their content. These categories will inform the development of main themes and sub-themes. The findings will help to further explain the impact of the intervention from multiple perspectives.

### Interim analyses {21b}

An interim analysis is not planned because the study poses minimal safety concerns and is being implemented within established healthcare facilities. The control group will continue receiving standard care, which helps minimise immediate safety and ethical concerns. Additionally, a complete dataset is required to properly assess the study outcomes.

### Methods for additional analyses (e.g. subgroup analyses) {20b}

Subgroup analyses will be conducted to explore the effectiveness of the intervention in relation to participants’ sociodemographic status, knowledge, and health-seeking behaviour, thus helping to further explain the primary outcome variable.

